### Secondary outcomes

The secondary outcomes will be the proportion of patients with good functional outcome (assessed by the mRS) in each group at 3 months after stroke onset; change in NIHSS scores from before RIC to after RIC; incidence of major adverse cardiovascular events (MACE), aspiration pneumonia, and all-cause mortality within 90 days after stroke onset; frequency of adverse RIC-related events; and proportion of patients with an mRS score of 0–1.

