### Sample size calculation

The target sample size is based on previous reports (Table 3). In this study, patients will be divided into three groups based on their neurological severity at enrollment, and the functional outcome at 3 months after stroke onset will be determined for each group. A good functional outcome will be defined as mRS scores of 0–1, 0–2, and 0–3 for the mild (NIHSS score at enrolment, 5–9), moderate (NIHSS score at enrolment, 10–14), and severe (NIHSS score at enrollment, 15–20) groups, respectively. We hypothesize that the rates of good functional outcome are 35 and 50% in the control and RIC groups, respectively; accordingly, with 80% power at the 5% significant level, a sample size of 334 patients is necessary. Furthermore, to account for an expected drop-out rate of 10% (e.g., withdrawal of consent, lost to follow-up), we plan to enroll a total of 400 patients.

**Table 3 T3:** Previous reports on the relationship between the NIHSS on admission and modified Rankin Scale at discharge or 3-months after stroke onset.

**References**	**Year**	**No. patients**	**NIHSS on admission, median (IQR)**	**Severity**	**Therapy**	**mRS (%)**						
						**0**	**1**	**2**	**3**	**0–1**	**0–2**	**0–3**
Thomalla et al. (1)	2018	249	6 (4–9)	Mild	Placebo	15	27	23	17	42	70	87
Lees et al. (14)	2006	847	14.5	Moderate	Placebo	11	20	12	13	31	43	58
Shuaib et al. (15)	2007	1,631	13.8	Moderate	Placebo	10	18	15	15	29	43	58
Shuaib et al. (16)	2011	249	10 (2–20)	Moderate	Control	0	32	12	17	32	44	59
Ginsberg et al. (17)	2013	419	11 (8–17)	Moderate	Placebo	15	23	18	15	38	56	71
Hess et al. (18)	2017	61	13 (8–20)	Moderate	Placebo					12	36	
Saver et al. (19)	2015	843	11.2 (9.8)	Moderate	Placebo	18	16	18	13	35	53	66
Elkins et al. (20)	2019	78	12 (2–29)	Moderate	Placebo	5	15	15	19	20	35	54
Kimura et al. (21)	2003	1,342	0–4							75		94
		1,020	5–9	Mild						41		75
		602	10–14	Moderate						20		46
		521	15–20	Severe						8		23
Goyal et al. (2)	2016	100	<10	Mild	Medical	14	13	28	15	28	55	71
		140	11–15	Moderate	Medical	7	11	16	20	17	34	54
		236	16–20	Severe	Medical	3	4	12	17	8	20	30
Hill et al. (22)	2020	556	17 (13–21)	Severe	Placebo	19	22	19	11	41	59	70
Nogueira et al. (23)	2018	99	17 (14–21)	Severe	Medical	4	5	4	16	9	13	29
Albers et al. (24)	2018	90	16 (12–21)	Severe	Medical	8	4	4	16	12	16	32

IQR, interquartile range; mRS, modified Rankin Scale; NIHSS, National Institutes of Health Stroke Scale; rt-PA, recombinant tissue-type plasminogen activator.

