### Statistical analysis of secondary outcomes

Percentage differences between the RIC and control groups in terms of the incidence of MACE, aspiration pneumonia, frequency of adverse RIC-related events, and all-cause mortality within 90 days will be evaluated using the Chi-square test. The change in NIHSS score from the time of enrollment to 1 week later will be evaluated in a two-sided analysis of variance, with α = 0.05 and power = 0.80. Additionally, with stratified analysis, we will compare the differences in the achievement rate (percentage) of the primary outcome in the RIC and control groups according to the severity of the disease at the time of enrollment (mild, moderate, and severe groups), age (dichotomized by the median of all enrolled patients), sex, presence of occlusion or severe stenosis of the main cerebral artery, treatment with rt-PA and/or EVT, and presence of diabetes mellitus.

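### The planned subgroup analysis compares RIC with control across 13 strata but states no test of whether the effect differs, so a uniform effect would usually look subgroup-specific if each stratum is judged on its own

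*Protocol article*

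**What the plan says.** The article's section on the statistical analysis of secondary outcomes sets out a stratified analysis of the primary outcome: "we will compare the differences in the achievement rate (percentage) of the primary outcome in the RIC and control groups according to the severity" of disease at enrolment (mild, moderate, severe). It then adds age cut at the overall median and "sex, presence of occlusion or severe stenosis of the main cerebral artery, treatment with rt-PA and/or EVT, and presence of diabetes mellitus".

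No arm-by-factor interaction, multiplicity rule or exploratory label is given. The sentence also attaches no named test and no P-value threshold to these comparisons. The Chi-square test in that section is tied to the event outcomes. The 0.05 threshold in the section on the primary outcome is tied to the regression.

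The Secondary outcomes section also lists "the proportion of patients with good functional outcome (assessed by the mRS) in each group at 3 months after stroke onset". Here the word group could mean severity class or treatment arm, so this item does not settle the matter.

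**The concern.** A significant result in one stratum and a non-significant one in another is not evidence that the effect differs. Each stratum holds only part of a sample sized for one overall comparison, so many strata will miss significance even if RIC works equally well in all of them.

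This matters here because the Introduction and Discussion present a severity-dependent definition of success as what sets the trial apart, and the Discussion says the result may bear on routine use. Readers will look at the severity classes. If those are read one P-value at a time, a benefit common to all patients could be reported as confined to one class, or a chance result as a real one.

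**Working it through.** **Inputs from the article**
- Planning rates: "the rates of good functional outcome are 35 and 50% in the control and RIC groups, respectively".
- Size: "with 80% power at the 5% significant level, a sample size of 334 patients is necessary"; 400 enrolled, 1:1, 10% drop-out, so 400 × 0.9 = 360 evaluable.
- Strata: severity 3 + five two-level factors × 2 = 13.

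**Assumptions**
- Two-sided P<0.05 in each stratum.
- Class mix, setting A: equal thirds, 35% vs 50% in every stratum, two-level factors at 30–50% prevalence.
- Class mix, setting B: the one Table 3 cohort reported in this trial's NIHSS bands, 1,020/602/521, which is 48/28/24%. Control success is 41% (mild, mRS 0–1) and 23% (severe, mRS 0–3) from its rows. The moderate row has no mRS 0–2 figure, so 35% is assumed. Two-level factors are at 25–50% prevalence.
- The factors are independent of one another in setting A.

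**1. The plan's own figure.** Per arm: (1.960 + 0.842)² × (0.35×0.65 + 0.50×0.50) / 0.15² = 7.849 × 0.4775 / 0.0225 = 166.6, rounded up to 167. The total is 334, as stated. (The pooled-variance formula gives 340.)

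**2. No effect anywhere, 13 within-stratum tests.** The expected number of false positives is 13 × 0.05 = 0.65. If the tests were independent, the chance of at least one would be 1 − 0.95¹³ = 48.7%. The strata reuse the same patients, so the tests overlap. Simulation with that overlap gives about 35% (35–36% across settings).

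**3. Uniform 15-point effect, power by severity class (setting B, 360 evaluable).** With m patients per arm in a class, power = Φ[(0.15 − 1.96·s₀)/s₁], where s₀ = √(2p̄(1−p̄)/m) and s₁ = √((p_C(1−p_C) + p_T(1−p_T))/m).

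| Class | Patients | Control → RIC | s₀ | s₁ | Power |
|---|---|---|---|---|---|
| Mild | 171 | 41% → 56% | 0.0764 | 0.0756 | 50% |
| Moderate | 101 | 35% → 50% | 0.0984 | 0.0972 | 33% |
| Severe | 88 | 23% → 38% | 0.0982 | 0.0968 | 33% |

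**4. How often the classes split.** The classes share no patients, so the probabilities multiply:
- all three significant: 0.50 × 0.33 × 0.33 ≈ 5%
- none significant: 0.50 × 0.67 × 0.67 ≈ 22%
- split: 100 − 5 − 22 ≈ 72% (unrounded)

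Simulation gives 74% in setting B with 360 evaluable (76% with 400), and 72% in setting A with 400 (71% with 360). In setting A each two-level factor splits in about 48–56% of trials.

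**5. The alternative: one interaction test per factor.** With no difference in effect, the chance of at least one spurious result among six is 1 − 0.95⁶ = 26.5%. Simulation with a heterogeneity test on the risk difference gives 27–28%, both with no effect and with a uniform effect.

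**6. What the alternative cannot do.** Take two equal halves of 400, with a benefit that differs by 15 points between them. The variance of each half's difference is about (0.2275 + 0.25)/100, so the standard error of the contrast is √(2 × 0.004775) = 0.098. Power is Φ(0.15/0.098 − 1.96) ≈ 34% (31% with 360).

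**The case against.** The strongest reply is that the article condenses a fuller protocol, and that interaction terms and forest plots usually sit in an analysis plan that is not shown. Silence on an interaction test would indeed be no finding by itself. But the article does more than stay silent: it names a stratified comparison, lists the factors and fixes the age cut. An analysis plan that followed this wording would inherit the weakness.

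Three stronger readings are tempting, and the document does not support them.
- **That the plan rules out testing for a difference in effect, or commits to 13 significance tests.** Within-stratum comparison is the more natural reading, but the wording does not strictly exclude comparing differences across strata, and it sets no P-value rule.
- **That chance findings are likely.** The figure is about one in three, and the alternative still carries about 27%. The main gain from changing is fewer false subgroup-specific readings, not the removal of multiplicity.
- **That the trial's main conclusion is at risk.** The subgroup factors are pre-specified and described with the secondary analyses. The severity-dependent thresholds serve one pooled endpoint, and no claim of benefit in a single class is planned. The primary test and its error rate are untouched.

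It is also fair to say that a pre-specified median split of age is legitimate. Treating age as continuous is a preference that saves information, not the correction of an error.

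**Conclusion.** The point holds in this limited form: a stratified RIC-versus-control comparison over 13 strata is fixed in the text, and no test of whether the effect differs is stated with it. If the strata are read by their own P<0.05, a uniform 15-point effect would make the severity classes disagree in about 72–74% of trials, against about 27% with any spurious result from six interaction tests. With no effect, at least one stratum would be falsely positive in about 35%.

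The 0.05 threshold, the class mix, the moderate-class control rate and the factor prevalences are assumptions. The two quite different class mixes give nearly the same answer. This is worth correcting before analysis, but it does not threaten the primary result.

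**What to change.** - State that each of the six factors is judged by an arm-by-factor interaction test in the regression with odds ratios already planned for the primary outcome.
- Keep severity as the three enrolment classes. Continuous NIHSS would fit poorly, because the definition of success changes in steps at NIHSS 10 and 15.
- Preferably enter age as continuous for the test. The median split can stay for display.
- Report each stratum's estimate with a 95% confidence interval, with no significance claim within a stratum.
- Label all subgroup results exploratory.

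The cost is wording only, with no added patients, visits or data. The trial gives up any claim of significance inside one subgroup. Interaction tests at this size have low power (about one in three for the 15-point contrast in step 6), so a non-significant interaction must not be reported as proof of a uniform effect.

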**Design and methods:**

This study is an investigator-initiated, multicenter, prospective, randomized, open-label, parallel-group clinical trial. The sample size is 400, comprising 200 patients who will receive RIC and 200 controls. The patients will be divided into three groups according to their National Institutes of Health Stroke Scale score at enrollment: 5–9, mild; 10–14, moderate; 15–20, severe. The RIC protocol will be comprised of four cycles, each consisting of 5 min of blood pressure cuff inflation (at 200 mmHg or 50 mmHg above the systolic blood pressure) followed by 5 min of reperfusion, with the cuff placed on the thigh on the unaffected side. The control group will only undergo blood pressure measurements before and after the intervention period. This trial is registered with the UMIN Clinical Trial Registry (https://www.umin.ac.jp/: UMIN000046225).

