### Patient population

We will recruit patients diagnosed as having had an acute ischemic stroke *via* brain MRI and/or CT. All 14 Japanese stroke centers and their prehospital regional centers will be invited to participate. The inclusion and exclusion criteria are listed in Table 1, and the baseline assessments and study procedures are provided in Table 2 and Figure 1. Participants need to show a defined ischemic lesion on magnetic resonance imaging (MRI). Patients who received alteplase treatment or mechanical thrombectomy can be enrolled 12 h after the intervention. All patients will provide written informed consent in the acute phase. If the research participant is an adult who is objectively judged to lack the capacity to give informed consent due to a speech or writing impairment caused by a stroke, the consent may be obtained from the legal representative.

**Table 1 T1:** Inclusion and exclusion criteria.

**Inclusion criteria**	**Exclusion criteria**
• Patients hospitalized in participating institutions	• mRS >2 before stroke onset
• Male and female patients (age range, 20–90 years)	• Planned intravenous rt-PA and/or EVT after registration
• Diagnosed as acute ischemic stroke by performing brain MRI and/or CT	• Within 12 h after rt-PA administration or EVT
• Within 48 h after stroke onset	• Systolic blood pressure ≥180 mmHg
• NIHSS scores range from 5 to 20 at registration	• History of PAD
• Tolerance to systemic blood pressure measurement and systolic blood pressure <180 mmHg	• Pregnant patients or patients suspected of being pregnant
	• Patients deemed unsuitable as participants by the investigator

CT, computed tomography; EVT, endovascular treatment; MRI, magnetic resonance imaging; NIHSS, National Institutes of Health Stroke Scale; PAD, peripheral arterial disease; rt-PA, recombinant tissue-type plasminogen activator.

**Table 2 T2:** Study procedures for eligible patients with acute ischemic stroke.

**Procedures/Data collection**	**Screening (days 0–1)**	**Registration/ Baseline visit 1 (day 1)**	**Visit 2 (day 3)**	**Visit 3 (day 7)**	**Visit 4 (day 30 or discharge)**	**Visit 5 (day 90 ±14 days)**

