**Enrollment**						
Informed consent	×					
Demographic characteristics	×					
Confirmation of patient background and medical history	×					
Randomization	×					

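### The RIC effect by age is examined only across a split at the enrolled median; if the effect changes roughly linearly with age, this gives up about 25% to 36% of the available information

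*Protocol article*

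**What the plan says.** The section on statistical analysis of secondary outcomes states that, "with stratified analysis, we will compare the differences in the achievement rate (percentage) of the primary outcome in the RIC and control groups", by severity at enrolment, age, sex, main-artery occlusion or severe stenosis, reperfusion treatment and diabetes. Age enters as "age (dichotomized by the median of all enrolled patients", that is, as two groups.

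Table 1 sets a wide eligible range: "Male and female patients (age range, 20–90 years". The procedures table (Table 2) lists "Demographic characteristics" at screening. The multiple regression described for the primary outcome yields odds ratios, but the article names no covariates or interaction terms for it. No analysis of the RIC effect over continuous age is described.

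**The concern.** Eligible ages span 70 years (90 − 20), but the plan reduces age to a single yes/no variable before looking at the RIC effect. Patients just either side of the median are contrasted in full, while patients decades apart on the same side are treated as alike. If the benefit of RIC rises or falls gradually with age, a two-group comparison estimates that trend less precisely than a model using the ages themselves.

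This is a separate matter from whether the subgroups are compared by a formal interaction test. A correct interaction test on the split variable has the same loss.

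What is at stake is limited: the trial's ability to say something useful about age as a modifier of the RIC effect. The sponsor chose to examine age, and the trial was sized only for the overall comparison, so information on subgroups is scarce to begin with.

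**Working it through.** **1. The plan's own figure.** The article gives no figure for the age subgroup. Its only sample-size figure is for the primary outcome: "the rates of good functional outcome are 35 and 50% in the control and RIC groups, respectively", and "with 80% power at the 5% significant level, a sample size of 334 patients is necessary". The two-sided two-proportion formula with unpooled variance gives, per arm,

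n = (1.960 + 0.842)² × (0.35 × 0.65 + 0.50 × 0.50) / 0.15² = 7.85 × 0.4775 / 0.0225 ≈ 166.6, so 167 per arm and 334 in total.

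This reproduces the stated number. The article plans to enrol 400 ("The sample size is 400, comprising 200 patients who will receive RIC and 200 controls") and expects 10% drop-out, so 400 × 0.90 = 360 patients are evaluable. The rates imply an odds ratio of (0.50/0.50) / (0.35/0.65) = 1.86, a log odds ratio of 0.62, and a control-arm log-odds of ln(0.35/0.65) = −0.62.

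**2. Information kept by a median split.** For an effect that is linear in age, the efficiency of the split relative to continuous age is the squared correlation between age and its above/below-median indicator. The article gives no age distribution, so several were assumed:

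| Assumed age distribution | Kept | Lost |
|---|---|---|
| Normal | 2/π = 0.637 | 36% |
| Truncated normal on 20–90 (means 65–75, SD 10–15) | 0.65–0.66 | 34–35% |
| Left-skewed on 20–90 | 0.64–0.65 | 35–36% |
| Uniform on 20–90 | 0.75 | 25% |

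In patients, 360 × 0.637 ≈ 229 for normal ages and 360 × 0.75 = 270 for uniform ages.

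A linear interaction that continuous age would detect with 80% power has a standardised effect of 1.960 + 0.842 = 2.802. After the split of a normal covariate this becomes 2.802 × √0.637 = 2.235, and the power is Φ(2.235 − 1.960) ≈ 61%.

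**3. Simulation at 360 patients.** Model: logit = −0.62 + 0.62·RIC − 0.5·age + b·age·RIC, with age standard normal and 1:1 allocation, and a Wald test of the interaction at 5%. The age effect of −0.5 per SD and the values of b are assumptions. The last column is exp(0.62 ± 2b).

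| b (log-odds per SD) | Power, continuous | Power, split | RIC odds ratio at −2 SD and +2 SD |
|---|---|---|---|
| 0 | about 5% | about 5% | 1.86, 1.86 |
| 0.2 | 14% | 10% | 1.25, 2.77 |
| 0.4 | 42% | 28% | 0.84, 4.14 |
| 0.6 | 76% | 58% | 0.56, 6.17 |

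Repeat runs differ by about one or two percentage points. A separate simulation with ages truncated normal on 20–90 (mean 72, SD 12 before truncation) agreed: 81% against 61% at 360 patients and 85% against 65% at 400, with false-positive rates of 4% to 5% for both methods.

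**4. A shape that favours the split.** If the RIC log-odds effect is instead a step of ±0.5 exactly at the median, power is 43% for the linear continuous term and 58% for the split.

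**The case against.** The strongest reply is that the loss is conditional. It needs an effect that is roughly linear in age, and its size depends on an age distribution that the article does not give. With a step at the median the ranking reverses. This stands, so the loss is stated as a range and under that condition.

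Second, the larger power gaps belong to strong interactions. At 0.4 and 0.6 log-odds per SD, the RIC effect changes direction within two SDs of the mean age. At 0.2 it does not, and there both analyses are nearly uninformative and the gain is about 4 points. This also stands.

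Third, the article describes a descriptive stratified comparison, with no interaction test or power claim for age. That limits the weight of the point but does not remove it, since the comparison is there to show whether the RIC effect differs by age.

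Fourth, a continuous model may be in the full plan, which is not shown. That is possible, and an omission alone would be no finding. The point rests on the form the article does fix for age.

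A reader might also infer that the median is an improper, data-driven cut and should give way to a round age. The documents do not support that. The rule is set in advance, does not depend on outcomes and gives balanced groups, and a round cut could be unbalanced. Nor can a mismatch with other RIC trials be shown, because the article gives no age cut from any of them.

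**Conclusion.** The point holds as a minor improvement. Under an effect roughly linear in age on the log-odds scale, the median split loses about 25% to 36% of the information on effect modification by age, with about a third the likely figure for the bell-shaped or left-skewed ages tried here. The practical gain from continuous age at about 360 patients runs from about 4 percentage points of power at 0.2 log-odds per SD to about 18 at 0.6.

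A reader might take this to mean that the split always wastes a third of the data, or that it undermines the trial's conclusions. Neither follows. The loss depends on the shape of the effect and on assumed ages. The analysis is secondary and not powered, the false-positive rate stays near 5% with either method, and the primary comparison is untouched. The article also makes no claim that age modifies the RIC effect; it only lists age as a factor to examine.

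**What to change.** In the section on statistical analysis of secondary outcomes, add a RIC-by-age interaction with age in years as a continuous term in a logistic model for the primary outcome. Use a spline to check linearity, plot the estimated RIC effect against age, and base any statement on effect modification by age on this model. The median split may stay in the descriptive subgroup table.

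The cost is one model term and a sentence of text. No extra patients or data are needed: finding the median already requires each patient's age. The downside is the linearity assumption, which the spline can check only with limited power at this sample size.

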## Discussion

Recently, clinical studies of RIC in patients with AIS are attracting a lot of attention. Indeed, several clinical studies are ongoing. The ongoing study by Purroy et al. is a study of acute stroke within 8 h of symptom onset with mRS 0–2 at 90 days as the primary outcome (25). The study of Blauenfeldt et al. is also an ongoing study of acute stroke within 4 h of symptom onset with mRS at 3 months as the primary outcome (26). To our knowledge, our study will be the first clinical trial to investigate the effect of RIC after ischemic stroke in Japan. RIC is safe, feasible, and offers similar clinical benefits to exercise therapy after stroke, while being less physically taxing for the patient (27, 28). This trial may help determine whether RIC should be recommended as a routine clinical strategy for patients with ischemic stroke. RIC may then become one of the choice for therapy in most patients with ischemic stroke. Regarding the pathophysiology for RIC, three potential mechanisms have been proposed: humoral, immunoregulatory, and neurotrophic factors. In addition, several studies indicate that the underlying protective mechanisms of remote ischemic conditioning are associated with its ability to attenuate production of free radicals, promote the cell survival pathway, modulate the immune system, or inhibit the apoptotic cell signaling pathways (29–33). However, these proposed theories still require confirmation.

To date, several clinical studies have evaluated the effectiveness of RIC in patients with acute ischemic stroke, and no study has confirmed its efficacy except for a small clinical trial. Recently, three published clinical studies reported that RIC performed in four cycles of 5 min of inflation and 5 min of deflation for only 1 day after stroke onset did not significantly reduce the brain infarct volume growth or improve the functional outcome at 3 months (10–12). Furthermore, a recent report by Landman et al. studies acute ischemic stroke within 24 h of onset with infarct size on day 4 after admission. In this study, RIC was repeated twice daily with at least 6 h in between and continued for the duration of hospitalization for a maximum of 4 days. However, on average, RIC was conducted for only 2 days and this study did not show significant reduction of the brain infarct size (34). One reason for the inconsistency regarding RIC's effectiveness may be the lack of an established RIC protocol. Previous study by An et al. demonstrated a favorable effect of RIC on the clinical outcome at 3 months using an RIC protocol of five cycles of cuff inflation (to 180 mmHg for 5 min) and deflation (for 3 min) twice per day throughout the duration of the hospitalization (mean, 11.2 days; range, 8–14 days) although this is very small study (35). Additionally, two published experimental studies found that repeated RIC for 14 consecutive days was associated with a smaller infarct size in an animal model for brain ischemia (36, 37). Of these two studies, the study by Ren et al. showed that a single episode of RIC afforded short-term protection including reduction of brain infarct size, while brain infarct size was further ameliorated when combined with repeated RIC during the 14 days after reperfusion (36). Furthermore, a recent animal model study reported that the number and duration of the cycles determined the efficacy of RIC (38). Specifically, two cycles of RIC were insufficient to decrease infarct size, whereas four, six, and eight cycles decreased the infarct size. Similarly, cycles with 2 or 5 min of ischemia decreased the infarct size, whereas cycles with 10 min of ischemia did not reduce the infarct size. In previous experimental studies, three to five 5-min cycles of RIC reduced the infarct size and improved the neurological deficit (33, 39, 40). Our previous experimental study also showed that four cycles of RIC, with each occlusion and release phase lasting 5 min, had efficacy in reducing the infarct volume (41). Based on these reports, it may be essential to perform RIC for a suitable number of cycles and consecutive days to achieve a good functional outcome. Therefore, we will perform four cycles of RIC, alternating 5 min of inflation and 5 min of deflation, repeated over 3–7 days.

The primary outcome of this trial will be good functional outcome at 3 months, determined by the mRS score. In most previous studies, the definition of a good functional outcome at 3 months (based on the mRS) was the same for all patients, regardless of the NIHSS score at stroke onset. Our study differs from previous studies in this respect. Referring to previous studies showing the relationship between NIHSS at admission and mRS at discharge or 3 months after stroke onset, our study will divide patients into three groups based on their neurological severity (assessed by the NIHSS) at enrollment into the trial and will use different target mRS scores to define a good outcome at 3 months according to the severity group. For the safety outcome, the analysis will be based on the entire randomized sample. This approach has been used in a recent comparative study and is considered reasonable given the excellent safety profile of RIC.

Finally, we aim to include 400 patients. In this study, the criteria were simplified to enroll a more significant number of patients with various types of strokes. Therefore, given that ~200 patients with ischemic stroke are admitted to our hospital each year, and since this is a multicenter study, we expect to be able to recruit 400 patients during a recruitment period of 2 years.

